### Interventions measures

Patients in the SHHS group will receive SHHS granules (10 g per bag), two bags at a time, three times a day, to be swallowed with warm water. The administration of LHQW granules (10 g per bag) will be the same as the SHHS group. The medication course was 7 days (the medication could be stopped in advance if the discharge standard was reached). It will be forbidden to receive other TCM for COVID-19 treatment during the treatment period, including TCM decoctions, granules, or proprietary Chinese medicine. The types, dosage, and cumulative time (including the start and end dates) of the combined therapy drugs should be recorded during the observation period. The intervention will be stopped if there are any severe adverse effects or withdrawal.

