### Primary outcomes

The primary outcome is the rate of recovery from four types of patients' self-reported clinical symptoms, including fever, coughing, sore throat and fatigue. It specifically refers to the proportion of patients who met the criteria at the baseline for specific clinical symptoms and achieved recovery at the end of treatment on the seventh day.

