### Secondary outcomes

The secondary outcomes are the recovery time of patients self-reported clinical symptoms, SARS-CoV-2 nucleic acid testing negative conversion time, and negative conversion rate, hospitalization time, antipyretic time, the incidence of severe patients, single symptom disappearance time, and disappearance rate.

Criteria for judging the curative effect:(1) Recovery time and cure rate of clinical symptoms: The recovery of clinical symptoms refers to the disappearance of the main symptoms, ie. fever, coughing, sore throat, and fatigue. The cure rate is defined as the proportion of patients whose clinical symptoms recovered after the end of treatment on the seventh day.(2) SARS-CoV-2 nucleic acid testing negative conversion time and negative conversion rate: Taking the first time of the two consecutive respiratory tract SARS-CoV-2 PCR negative tests (sampling interval at least 1 d) as the SARS-CoV-2 PCR testing negative time (the SARS-CoV-2 nucleic acid testing negative conversion time equals the SARS-CoV-2 PCR testing negative time–the diagnosis time of the patient).(3) Hospitalization time: the time from patient admission to discharge. The discharge standard refers to the release from isolation or discharge criterion of the protocol for diagnosing and treating novel coronavirus pneumonia (9th edition).(4) Antipyretic time: The body temperature is less than 37.4°C after treatment, for 24 h or more.(5) The conversion rate of turning to severe patients: the proportion of patients who develop severe infection 7 days after taking medicine.

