## Statistical analysis plan

### Statistical methods

The statistical analysis plan will comply with the guidelines for the content of statistical analysis plans in clinical trials (Gamble et al., 2017). (**Additional File 3**). After finishing the trial, all statistical analysis tests will be conducted using SAS (version 9.4; SAS Inc., Cary, NC, USA) and one-sided tests with a nominal alpha level of 0.025. All confidence intervals (Cls) will be stated at the 95 confidence level. To assess non-inferiority, the CI lower limit of the difference between groups will be compared with a predefined non-inferiority limit. Non-inferiority could only be declared when the 95% CI lower limit of the difference between groups is not larger than the non-inferiority threshold of 10%.

Continuous outcomes will be described by calculating the mean, standard deviation, median, and minimum and maximum values. The means and standard deviations are reported for normal continuous data. For non-normally distributed continuous variables, the median and interquartile ranges are given. The frequency and proportion of each category are displayed as counting indications.

Between-group comparisons are performed using an independent two-sample t-test (normality, homogeneity of variance) or the Wilcoxon rank-sum test (non-normality, heterogeneity of variance). The paired t-test is used for comparisons within normally distributed groups, and the paired rank-sum test is used for comparisons within non-normally distributed groups. For count metrics, the χ^2^ test or Fisher's exact probability will be required, whereas, for categorical variables, the Wilcoxon rank-sum test will be utilized. Repeated measured outcomes are applied to a generalized linear mixed model analysis.

In patients where baseline indicators are unbalanced, an adjustment to the efficacy contrast of variables such as age, sex, and concurrent therapy is required. The covariance approach is employed for continuous variables, and for count or rank data, logistic regression analysis is performed.

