### Definition of analysis sets

(1) Full analysis set (FAS): All participants randomly assigned to the group, use the medicine at least once, and have at least one visit will be analyzed using intention-to-treat analysis of the entire dataset.(2) Per protocol set (PPS): This includes all participants who comply with the research protocol, which have no missing data on important baseline variables and primary outcome. Major violations on concomitant medicine and extremely lower compliance will be considered to be excluded from PPS.(3) Safety set (SS): All randomized participants could be included in SS if they have used at least one dose of drugs and have completed at least a one-time safety assessment. Impution will not be conducted for safety outcomes in SS.

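### Antipyretic time is scored without regard to antipyretic use, so this secondary outcome can date a drug response instead of the end of fever; the primary outcome is exposed only in part, and by an unknown amount

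*Protocol article*

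**What the plan says.** Under Secondary outcomes, criterion (4) reads "Antipyretic time: The body temperature is less than 37.4°C after treatment, for 24 h or more". Criterion (1) in the same section defines recovery separately: "The recovery of clinical symptoms refers to the disappearance of the main symptoms, ie. fever, coughing, sore throat, and fatigue". The Primary outcomes section takes the primary from the patient's own report: "the rate of recovery from four types of patients' self-reported clinical symptoms, including fever, coughing, sore throat and fatigue". Table 4 lists time to recovery of fever and antipyretic time as separate rows.

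On co-treatment, Interventions measures states "It will be forbidden to receive other TCM for COVID-19 treatment during the treatment period". It names no antipyretic or analgesic. It also asks for a record: "The types, dosage, and cumulative time (including the start and end dates) of the combined therapy drugs should be recorded during the observation period". Table 1 schedules combined drugs at screening and on each of days 1 to 8.

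Two further passages touch on co-medication. Statistical methods says "In patients where baseline indicators are unbalanced, an adjustment to the efficacy contrast of variables such as age, sex, and concurrent therapy is required". Definition of analysis sets says "Major violations on concomitant medicine and extremely lower compliance will be considered to be excluded from PPS".

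**The concern.** Antipyretic time is meant to show how soon fever ends on the study drug. As worded, it can instead show how soon temperature fell after an ordinary antipyretic. If many patients take one, the two arms may look alike because both received the same symptomatic drug.

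The primary outcome has a related weakness. A patient whose fever or sore throat is held down by a drug on day 7 may truthfully report that it has gone. In a non-inferiority trial, anything that hides non-recovery equally in both arms shrinks a true deficit and makes non-inferiority easier to declare. The trial is open-label, so symptomatic drugs may also be used unequally by arm. Blinded assessment does not prevent that.

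**Working it through.** **1. Does another passage close the gap?**

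- *Prohibited treatment.* Only other TCM for COVID-19 is excluded, so antipyretics are not ruled out.
- *Covariate adjustment.* It is tied to imbalance in baseline indicators. Antipyretic use after randomization is not a baseline indicator.
- *Per-protocol exclusion.* It concerns major violations. Use of a drug that is not prohibited is not evidently a violation.
- *Table 2.* The co-medication rows are antiviral, anti-infective, Chinese patent medicine and others. None is for antipyretics.
- *Recording.* Types, doses and start and end dates are collected, but no outcome definition refers to them.

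None of these closes the gap for criterion (4).

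**2. The plan's own figure.** Inputs from Sample size: LHQW 87%, SHHS 90%, margin 10 points, one-sided 0.025, power 80%. With the unpooled normal approximation,

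n per arm = (1.960 + 0.842)² × (0.87×0.13 + 0.90×0.10) / (0.03 + 0.10)² = 94.3.

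The article states 94 per arm, which agrees apart from rounding; power at 94 is 79.9%. Allowing for 20% dropout, 188/0.8 = 235, which the planned 240 covers. If 20% do drop out, 240 × 0.8 = 192 remain, or 96 per arm. The sample size is not in question here; the same approximation is used below.

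**3. Illustration for the primary outcome.** The documents give no rate of antipyretic use, so the masked share s is an assumption. Put SHHS exactly at the margin: true recovery 77% against 87%, so non-recovery 23% against 13%. If a share s of non-recovered patients in each arm is scored as recovered:

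- observed SHHS = 0.77 + 0.23s
- observed LHQW = 0.87 + 0.13s
- observed difference = −0.10 × (1 − s)
- P(declare non-inferiority) = Φ[(0.10 + difference)/SE − 1.960], with SE² = [p₁(1−p₁) + p₂(1−p₂)]/n.

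For example, s = 0.2 and n = 120 give 81.6% against 89.6%, a difference of −8 points, SE = 0.0450, and Φ(0.02/0.0450 − 1.960) = 6.5%.

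| Masked share | Observed difference (points) | False non-inferiority, 120 per arm | 96 per arm |
|---|---|---|---|
| 0 | −10.0 | 2.5% | 2.5% |
| 10% in both arms | −9.0 | 4.0% | 3.8% |
| 20% in both arms | −8.0 | 6.5% | 5.9% |
| 30% in both arms | −7.0 | 10.5% | 9.2% |
| 20% in SHHS only | −5.4 | 16.4% | 14.0% |
| 20% in LHQW only | −12.6 | 0.6% | 0.7% |

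**4. What limits s.** Recovery is defined over fever, cough, sore throat and fatigue together. Masking fever or sore throat changes a patient's score only if neither cough nor fatigue remains. The table treats every non-recovered patient as maskable, so its larger values are upper bounds, not estimates.

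**The case against.** A reader might infer that the 37.4°C rule for 24 h also defines fever recovery in the primary outcome, so that a temperature below it on an antipyretic at day 7 makes a recovered patient, and that the non-inferiority result is pulled in one direction. The documents do not support this. The temperature rule belongs to antipyretic time alone. The primary rests on self-reported disappearance, with no threshold or duration. The 10-point margin was set for the symptom recovery rate, so criterion (4) does not drive the non-inferiority conclusion. The last two table rows show that the direction depends on which arm has more masking.

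Nor is antipyretic time distorted in every antipyretic user. The criterion asks for 24 h or more, so a brief dip does not qualify, and a patient whose fever was ending anyway is unaffected.

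Two further objections carry weight. Scoring outcomes regardless of permitted co-medication is a legitimate treatment-policy choice, whereas counting every recent user as a primary failure would bring its own bias under unequal open-label prescribing. That is a reason to leave the primary definition alone. Also, an article condenses a fuller protocol, and detailed scoring may sit there. This excuses an absent detail. Criterion (4), however, is a stated operational definition, complete with threshold and duration, and applied as written it admits suppressed fever.

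**Conclusion.** The point holds for antipyretic time: as defined, it can date the response to an antipyretic, and nothing else in the article corrects this. How many patients are affected cannot be known from the documents.

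For the primary outcome, the exposure is narrower and its direction conditional. It runs through self-report of fever and sore throat, in patients with no other main symptom left. The range of 4.0% to 10.5% rests on three assumptions: a true deficit exactly at the margin, equal masking of 10% to 30% of all non-recovered patients, and 120 analysed per arm. It shows what could be at stake and does not predict an error rate. A claim that the primary comparison is biased toward non-inferiority as such would go too far.

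**What to change.** - **Criterion (4), Secondary outcomes.** Count antipyretic time as reached only when the temperature criterion is met over a period with no antipyretic recorded. Use calendar days from the combined-drug start and end dates, because the article asks for dates and not clock times.
- **Primary outcome.** Keep the definition. Pre-specify a sensitivity analysis in which a patient with an antipyretic or analgesic recorded on the day of the day-7 assessment, or the day before, counts as not recovered for fever or sore throat.
- **Reporting.** Tabulate such use by arm, so that a reader can judge whether any masking was similar or unequal.

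The cost is one sentence in the outcome definition, one extra analysis and one table, all from data already planned. Antipyretic times will be somewhat longer, including in some patients who took the drug for another reason. The change affects scoring only, not the treatment that patients may receive.

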**Methods and analysis:** The study was designed as a 7-day, randomized, parallel controlled, open-label, noninferiority clinical trial of positive drugs. A total of 240 patients with mild and moderate COVID-19 will be enrolled and randomly assigned to receive SanHanHuaShi granules or LianHuaQingWen granules treatment in a 1:1 ratio. Disease classification, vital signs, SARS-CoV-2 nucleic acid testing, symptoms, medications, adverse events, and safety evaluations will be recorded at each visit. The primary outcome will be the clinical symptom recovery rate. Secondary outcomes will include the recovery time of clinical symptoms, negative conversion time of SARS-CoV-2 nucleic acid test negative conversion rate, hospitalization time, antipyretic time, rate of conversion to severe patients, and time and rate of single symptom recovery. Adverse incidents and safety assessments will be documented. All data will be analyzed using a predetermined statistical analysis plan, including our method for imputation of missing data, primary and secondary outcome analyses, and safety outcomes.

**Discussion:** The results of this study will provide robust evidence to confirm the effectiveness and safety of SHHS in the treatment of COVID-19.

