### Withdrawal criteria and termination criteria

First, the investigator's decision to withdraw the patient is based on the following principles: 1) during the clinical trial, the patients develop diseases that are not suitable for further study; 2) patients with adverse events or serious adverse events are not suitable to continue the study, and 3) other conditions that the researchers believe will harm the health of the patients by continuing the study.

Second, patients can and should withdraw if they are unwilling to continue with the clinical trial. According to the provisions of the informed consent form, participants can withdraw at any time during the study. If patients have not explicitly proposed to withdraw but no longer accept medication and testing, as well as loss to follow-up, are regarded as 'withdrawal'. The reasons for withdrawal should be known and recorded as precisely as possible. Examples include consciously being unable to tolerate adverse events, inability to continue clinical research due to other reasons, or loss to follow-up without explaining the reasons. In electronic case report forms (eCRFs), the reasons for dropout will be recorded and the data analysis will include their last record.

Third, when reviewing the data prior to statistical analysis, it is up to the principal investigator (PI) and statisticians to judge whether an individual case is excluded. If one of the following events occurs, the two sides should consider whether the patient should be excluded based on the study's progress and the reasons for withdrawal and provide a detailed explanation: 1) After randomization, individuals not meeting the selection criteria or meeting the exclusion criteria of the research proposal are found; 2) The failure to take at least one dose of trial medication and the lack of any data post-randomization.

Fourth, the conditions for stopping early are as follows: 1) if a high incidence of serious adverse events is found during the research, the study should be suspended in time; 2) if during the research, significant mistakes are found in the research proposal or there are serious deviations in its implementation, making it difficult to evaluate the efficacy of drugs, the research should be stopped; 3) the ethics committee requests to suspend or terminate the research; 4) the administrative department cancels the research.

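### The primary recovery rule counts only four symptoms and carries a dropout's last record forward, so a patient who turns severe, dies or is withdrawn for worsening can be scored as recovered

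*Protocol article*

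**What the plan says.** **Primary outcome.** Under Primary outcomes: "The primary outcome is the rate of recovery from four types of patients' self-reported clinical symptoms, including fever, coughing, sore throat and fatigue". A responder is a patient with qualifying symptoms at baseline who "achieved recovery at the end of treatment on the seventh day". Criterion (1) under Secondary outcomes gives the rule: "The recovery of clinical symptoms refers to the disappearance of the main symptoms, ie. fever, coughing, sore throat, and fatigue". Neither place sets a condition on disease severity or survival.

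**Dropouts and missing values.** Under Withdrawal criteria and termination criteria, the investigator may withdraw a patient when "during the clinical trial, the patients develop diseases that are not suitable for further study". For dropouts, "the reasons for dropout will be recorded and the data analysis will include their last record". Imputation of missing data fixes last observation carried forward (LOCF) for both primary and secondary outcomes.

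**Severe conversion.** The list of secondary outcomes names "the incidence of severe patients". Criterion (5) defines it as "the proportion of patients who develop severe infection 7 days after taking medicine".

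**Data collected.** The Abstract states: "Disease classification, vital signs, SARS-CoV-2 nucleic acid testing, symptoms, medications, adverse events, and safety evaluations will be recorded at each visit". Table 1 schedules clinical assessment at baseline and on days 1 to 8. Shortness of breath appears in Tables 2 and 4 but is not one of the four symptoms in the recovery rule.

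**The concern.** A patient whose COVID-19 has become severe, or who has died, has not recovered in any useful sense, yet nothing in the stated rule prevents that score. The inclusion criteria admit patients with as few as one of the four symptoms. A patient who enters with only a sore throat, loses it, then becomes breathless and severe without fever, cough or fatigue meets the definition of recovery.

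The missing-data rule adds a second route. If a patient is withdrawn for worsening, or dies, and the last symptom record shows the four symptoms absent, that record becomes the day-7 result.

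Two features of the trial make this matter. It is a non-inferiority trial, so failures scored as successes in the test arm push towards the favourable conclusion. And the case for SHHS rests on progression: the Introduction cites a retrospective cohort in which fewer mild and moderate cases turned severe, and the Discussion says a non-inferiority finding would confirm an effect on severe disease as well as on symptoms. A primary endpoint that can count a severe case as a success does not support that claim.

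**Working it through.** **1. The plan's own figure.** Inputs from Sample size: LHQW 87%, SHHS 90%, margin 10 points, one-sided alpha 0.025, power 80%.

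n per arm = [0.87 × 0.13 + 0.90 × 0.10] × (1.960 + 0.842)² / (0.10 + 0.03)² = 0.2031 × 7.849 / 0.0169 = 94.3.

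The stated 94 per arm reproduces (95 if rounded up; power at 94 is 79.9%). With 20% dropout, 188 / 0.8 = 235, and the plan enrols 240. The sample size is not in dispute. The 87% and 90% are planned rates of symptom recovery.

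**2. How the rule scores a patient who progresses.** This follows from the recovery definition and the LOCF rule together.

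| Course | Four symptoms on day 7 or in last record | Primary score as written |
|---|---|---|
| Turns severe, stays in the study | all absent | recovered |
| Turns severe, stays in the study | any present | not recovered |
| Withdrawn for worsening, or dies, before day 7 | all absent in last record | recovered, by LOCF |
| Withdrawn for worsening, or dies, before day 7 | any present in last record | not recovered |

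The error arises in the first and third rows only. The per-protocol set requires a non-missing primary outcome, so a patient in the third row would be imputed as recovered in the full analysis set and could be left out of the per-protocol set. Neither analysis would then record a failure.

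**3. Size, under an assumption.** The documents give no rate of severe conversion. Assume k excess SHHS patients wrongly scored as recovered, k = 1 to 3, with 120 per arm and true rates at the margin (87% versus 77%). The apparent SHHS rate is then 0.77 + k/120. With a Wald interval:

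SE = √{[0.87 × 0.13 + p(1 − p)] / 120}, with p = 0.77 + k/120

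P(false non-inferiority) = Φ[(k/120)/SE − 1.96]

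| k | Shift (points) | SE | Argument of Φ | P(false non-inferiority) |
|---|---|---|---|---|
| 0 | 0 | 0.0492 | −1.960 | 2.5% |
| 1 | 0.83 | 0.0488 | −1.789 | 3.7% |
| 2 | 1.67 | 0.0484 | −1.616 | 5.3% |
| 3 | 2.50 | 0.0480 | −1.439 | 7.5% |

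Three such patients use up a quarter of the 10-point margin.

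**4. Cost of correcting the score.** Assume that 1%, 2% or 5% of patients in both arms are recoded from recovered to non-recovered. The rates become 86/89%, 85/88% and 82/85%. The step 1 formula then needs 102, 109 and 128 per arm, and power at 94 per arm is 77%, 74% and 67%, against 79.9% with no recoding.

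**5. The severe-conversion window.** Criterion (5) uses a verb of onset (develop), its label speaks of conversion, and the list of secondary outcomes calls it an incidence. All three describe an event during follow-up. Disease classification is recorded at each visit, so a conversion on day 3 is in the data if the patient was assessed. What is unclear is whether the phrase about 7 days means within that period or at its end, and how a patient withdrawn for progression is counted.

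**The case against.** Five points can be made against this.

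- **Symptom recovery and severity are deliberately separate.** Severe conversion is reported by arm in both analysis sets (Table 4), and death and life-threatening events fall under adverse events. This stands as far as it goes: progression would be visible elsewhere. It does not change the score in the primary comparison, on which non-inferiority is declared.
- **Handling of such events is often left to a fuller document.** That is true, and the full plan is not shown. But the article is not silent: it states a recovery rule and an LOCF rule, and the two together produce the wrong score.
- **Withdrawal for progression is not named.** The withdrawal clause speaks only of diseases unsuitable for further study, and a patient withdrawn for progression would usually have that recorded. This stands for the severe-conversion outcome, where carrying the last record forward would usually carry the severe classification. It does not help the primary outcome, which reads only the four symptoms.
- **The affected patient may be rare.** Many patients who turn severe will still report fever, cough or fatigue. This stands, and the documents give no frequency.
- **Changing a primary endpoint after recruitment began is not trivial.** Recruitment started in March 2022 in an open-label trial. This stands as a reason to make the change before any unblinded look at the data.

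A reader might also infer that criterion (5) measures only whether a patient is severe on day 7, so that earlier progression is lost, or that progressors disappear from both endpoints. The documents do not support either reading, for the reasons in step 5 of the working.

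**Conclusion.** The point holds for the primary outcome. As written, a patient who progresses to severe disease, dies or is withdrawn for worsening counts as recovered whenever the four symptoms are absent on day 7 or in the last record, and the error favours the arm with more progression.

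Its size cannot be taken from the documents. The range of about 3.7% to 7.5% for false non-inferiority, against 2.5%, rests on four assumptions: 1 to 3 excess progressors, all in the SHHS arm, all free of the four symptoms, and a true deficit of exactly 10 points. If the misclassification is equal in both arms, the rate difference is not shifted, although both recovery rates are overstated.

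For severe conversion only a clarification is needed. The outcome is described as an incident event and the daily data to support it are planned; its time window is loosely worded. This is worth correcting now because the correction is cheap, but it does not show that the trial's result would be wrong.

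**What to change.** 1. In Primary outcomes and criterion (1), add that conversion to severe or critical disease, death, or withdrawal for worsening, at any time from first dose to the day-7 assessment, counts as non-recovered whatever the symptom record shows.
2. In Imputation of missing data, exempt these patients from LOCF for the primary outcome.
3. Reword criterion (5) as any conversion to severe disease, or death, from first dose through day 7, with withdrawal for progression counted as an event and not replaced by an earlier mild or moderate classification.

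No new data are needed: disease classification is already recorded at each visit, and the reason for dropout must be recorded. Recovery rates would fall somewhat below the 87% and 90% used for planning, with the loss of power shown in step 4 of the working if progressors are not rare. The sponsor should check the planning rates against the revised definition and date the change before any comparison by arm.
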